**Quality assurance**

The treatment protocol will be performed by two skilled researchers in the field of physical therapy/physical education who have previously performed this protocol with patients with neurodegenerative diseases (Spinocerebellar ataxia and Parkinson's disease) and will not be aware of the results of the initial evaluations of the patients who will undergo the interventions.

**Assessment of results**

The participants will be evaluated by an independent examiner who will be blinded to the allocation to the different groups. The primary outcomes will be evaluated with each of the assessment tools, considering an improvement in the performance in the comparison of the pre-intervention and post-intervention assessment:

PPA: quantifies the risk of falls.

Dynamometer: verification of improvement in muscle strength;

WHOQOL-Bref: improvement in perceived quality of life in different domains;

BBS: analysis of balance status;

ABC: like BBS, verifies balance, but related to activities of daily living;

VADL: investigates impact of dizziness and balance on degree of dependence;

MMSE: measures degree of cognitive impairment;

TUG test: measures risk of falls related to muscle weakness;

FES-I: investigates fear of falling;

VAS: quantifies pain intensity.

The secondary outcomes will quantify the improvement in performance on the assessment. For such, a specific questionnaire will be administered for each assessment.

Secondary outcome 1: Improved locomotion capacity, increased stability during gait, reduction in gait deviations; evaluated using TUG test and BBS.

Secondary outcome 2: Increased spatial orientation capacity; evaluated by PPA, WHOQOL-Bref, ABC scale and MMSE.

Secondary outcome 3: Reduction in falls;evaluated by FES-I, ABC scale, VADL scale and dynamometer.

Secondary outcome 4: Improved capacity to perform activities of daily living, generating self-confidence that will lead to positive gains in aspects of family, social and professional life; evaluated by WHOQOL-Bref, VAS and VADL scale.

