**Study population**

Forty patients with a diagnosis of HSP will be recruited from the hospital of the Federal University of Parana in the city of Curitiba, Brazil. To participate, the volunteers must meet the following eligibility criteria:

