**Lafayette dynamometer**

The Lafayette dynamometer^13,14^ is a portable device for the objective quantification of muscle strength based on the assessment of maximum voluntary isometric contraction^15^. Applicable to all segments of the body, measures peak force, duration of peak force, force (kgf) between selected intervals, mean force, total test time and peak torque.

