**Vestibular Disorders Activities of Daily Living (VADL) scale**

The VADL scale was developed by Cohen and Kimball^23^ to assess the impact of dizziness and imbalance on the performance of activities of daily living among individuals with vestibular disorders. The scale involves 28 activities divided into three dimensions: functional, locomotion and instrumental. The total VADL and dimension scores are determined by the median of the activity scores, with higher scores denoting greater dependence and disability^24^. The translation of the VADL from English into Brazilian Portuguese was performed following the guidelines of the Process of Cross-Cultural Adaptation^25^.The Brazilian version had adequate reliability and is a new assessment tool in the country for investigating functional capacity in individuals with vestibulopathies as well as guiding therapeutic planning, particularly vestibular rehabilitation^26^.

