**Data analysis**

Data analysis will involve repeated-measures ANOVA with the level of significance set at 5%.

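### Ten unranked primary outcomes share one 5% level with no success rule: if each gets one test and any one counts, the risk of a false primary success is up to about 40%

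*Protocol*

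**What the plan says.** Under Assessment of results the Protocol states: "The primary outcomes will be evaluated with each of the assessment tools". It then lists PPA, dynamometer, WHOQOL-Bref, BBS, ABC, VADL, MMSE, TUG, FES-I and VAS. No instrument is put first, none are combined, and there is no rule that all must succeed.

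The Data analysis section is one sentence: "Data analysis will involve repeated-measures ANOVA with the level of significance set at 5" per cent. It names neither the ANOVA effect of interest nor the number of tests that share the 5%.

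The four secondary outcomes use the same instruments:

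- Outcome 1: TUG and BBS.
- Outcome 2: PPA, WHOQOL-Bref, ABC and MMSE.
- Outcome 3: FES-I, ABC, VADL and dynamometer.
- Outcome 4: WHOQOL-Bref, VAS and VADL.

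Together these cover all ten primary instruments.

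Several instruments can yield more than one score. The dynamometer "measures peak force, duration of peak force, force (kgf) between selected intervals, mean force, total test time and peak torque". For VADL, "The total VADL and dimension scores are determined by the median of the activity scores", with three dimensions. WHOQOL-Bref is to be read across domains whose number is not given.

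**The concern.** The instruments cover fall risk, strength, quality of life, balance, confidence, daily activities, cognition, fear of falling and pain. With ten primaries of equal standing and no success rule, nothing in the text prevents one significant instrument from being presented as a positive primary result. The 5% level would then describe a single test and not the trial's risk of a false claim.

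The secondary tier offers no protection, because it contains nothing that is not already primary. The Conclusion section also presents the trial as able to settle the question of effectiveness, so the exposure cannot be set aside on the ground that the study is only exploratory.

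**Working it through.** The Protocol gives no power, sample-size calculation or familywise error rate, so there is no stated figure to reproduce.

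**Inputs from the Protocol**

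- Ten primary instruments (Assessment of results).
- Significance level 0.05, with no split or adjustment stated (Data analysis).
- "Forty patients with a diagnosis of HSP will be recruited" (Study population), 20 per group (Randomization).
- Two time points: the success criterion is a "comparison of the pre-intervention and post-intervention assessment".

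**Assumptions**

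- One two-sided test per instrument. Sidedness is not stated, but with two groups and two time points the group-by-time F test has one numerator degree of freedom and is equivalent to a two-sided t test on change scores.
- Any one significant instrument counts as success.
- Correlations between the ten test statistics are not given, so a common value from 0 to 0.9 was tried.

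**Familywise error when all ten nulls are true**

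- Expected number of false positives: 10 × 0.05 = 0.5.
- Independent tests: 1 − 0.95^10 = 1 − 0.599 = 0.401. By Šidák's inequality this is also the ceiling for jointly normal two-sided statistics, whatever their correlation.
- Correlated tests, by simulation:

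| Common correlation | Normal statistics, 400,000 draws | t tests on change scores, 20 v 20, 40,000 replicates |
|---|---|---|
| 0 | 40.1% (exact) | 40.0% |
| 0.3 | 35.1% | 35.2% |
| 0.5 | 28.6% | 29.4% |
| 0.7 | 21.4% | 22.0% |
| 0.9 | not run | 13.0% |

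Even at 0.9 the rate is more than twice the nominal 5%.

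**After correction**

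- Holm tests the smallest p-value at 0.05/10 = 0.005. Under independence with all nulls true, the familywise error is 1 − 0.995^10 = 0.049. It is at most 5% under any dependence.
- Detectable effect at 80% power (two-sample t test on change scores, 20 per group, in SDs of change): 0.909 at a level of 0.05 and 1.217 at 0.005, a ratio of 1.217/0.909 = 1.34.

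**The case against.** The main objection is that multiplicity control is commonly left to a statistical analysis plan, and none is shown. The Protocol does not literally say that each instrument is tested at 5%, does not exclude an adjustment, and nowhere says that one significant result suffices. This stands as a limit on the figures: the 40% depends on a reading of the text, not on a stated success rule. It does not remove the point, because the choice of primary outcomes is made in the Protocol itself, and what it fixes is ten unranked primaries beside one 5% level.

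A second objection is that independence is implausible. PPA, BBS and TUG all grade fall risk, and the Protocol itself likens ABC to BBS. This also stands, and makes the correlated figures more realistic than the ceiling. Those correlations are assumed, however, and none of the values tried brings the rate near 5%.

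In the other direction, a reader might infer a larger family: six dynamometer parameters, four VADL scores (total plus three dimensions) and the other eight instruments once each make 6 + 4 + 8 = 18 tests, and 1 − 0.95^18 = 0.603. The documents do not support 60% as the trial's error rate. The dynamometer passage describes what the device can record, and the VADL passage how the scale is scored; neither lists planned tests. Assessment of results gives the dynamometer a single purpose, improvement in strength. What remains is that the number of scores per instrument is not settled.

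A reader might also infer that BBS is the obvious sole primary, since the games were chosen to favour balance. The Treatment section gives the same five balance games to both groups, and the randomized difference is the four strength games. The Protocol links those exercises to balance too, but that does not single out BBS. The choice belongs to the investigators.

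**Conclusion.** The point holds in a conditional form. The Protocol fixes ten unranked primary outcomes, one 5% level and no definition of trial success, and its secondary outcomes reuse all ten instruments. With one two-sided test per instrument and any single success counting, the chance of at least one false primary success is at most about 40%. At assumed common correlations of 0.3 to 0.7 it is roughly 35% down to 21%. Separate testing of WHOQOL-Bref domains, VADL dimensions or several dynamometer measures would raise it by an amount that cannot be fixed from the document. This should be corrected before the analysis, since the text as written would let a claim with a false-positive risk several times the nominal level stand as the primary result.

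**What to change.** **Preferred.** Before outcome data are examined, name one score for each of the ten instruments. State that primary claims rest on Holm-adjusted p-values across the ten, for the between-group (group-by-time) effect. Naming that effect matters because both groups train, so change over time alone does not isolate the added strength games.

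**Alternative.** The investigators name one examiner-measured instrument of their choice as the sole primary and make the other nine secondary. The Timeline section says recruitment is complete and analysis is due in 2021, so this is credible only if a dated amendment can show that no outcome data had been seen. Otherwise it becomes selective choice of outcome, and Holm across the ten is the sound option.

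**Cost.** Holm needs no new data, but the effect detectable with 80% power at its first step rises from about 0.91 to 1.22 SD of change, under the assumptions above; later steps are less strict. The single-primary route avoids that loss but requires amending the Protocol and its registry entry.

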**Randomization**

Prior to the intervention, the volunteers will be randomly allocated to two different groups. Randomization will be performed by an independent researcher using a simple lottery system with sealed opaque envelopes immediately after the baseline assessment. The volunteers will be considered participants in the study the moment the envelope is opened. The participants will be randomized to receive the following distinct interventions:

Group I: Twenty volunteers will undergo VR with virtual reality (balance games) using the Wii® console, Wii-Remote and Wii Balance Board (Nintendo).

Group II: Twenty volunteers will undergo VR with virtual reality (balance games and muscle strength games) using the Wii® console, Wii-Remote and Wii Balance Board (Nintendo).

The games will last from 30 minutes to one hour, with sessions twice a week for 10 weeks (total: 20 sessions).

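### The primary criterion is worded as pre-to-post improvement and no between-group term is made decisive, so a time effect shared by both arms would satisfy it

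*Protocol*

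**What the plan says.** - **Randomised comparison.** The Randomization section states: "Prior to the intervention, the volunteers will be randomly allocated to two different groups". There are 20 patients per arm. Under Treatment, both groups play the same five balance games and Group II also plays four strength games.
- **Primary criterion.** Assessment of results lists ten tools as primary, each judged "considering an improvement in the performance in the comparison of the pre-intervention and post-intervention assessment".
- **Secondary criterion.** The same section continues: "The secondary outcomes will quantify the improvement in performance on the assessment". Neither sentence mentions a comparison of Group I with Group II, and no other section does so.
- **Analysis.** The whole Data analysis section reads: "Data analysis will involve repeated-measures ANOVA with the level of significance set at 5" per cent. It does not say whether time, group or group-by-time carries the conclusion.
- **Conclusion.** The Conclusion section promises a definitive answer on the effectiveness of the virtual-reality programme, which both arms receive.

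**The concern.** The only randomised question is whether strength games add anything to balance games. The only criterion written down concerns change over time within patients. Practice on the tests, regression to the mean, attention and the shared balance training all contribute to that change in both arms, and none of them measures the randomised difference.

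The safeguards listed under Control of bias, such as concealed allocation and analysis by intention to treat, protect a comparison between arms. They do nothing for a comparison of before with after. If the result is read off the time effect, the trial can report a positive primary finding that owes nothing to randomisation, and the Conclusion section as worded would accept it as evidence for the programme.

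**Working it through.** **Inputs from the Protocol.** 40 patients, 20 per arm (Study population, Randomization); two assessments, before rehabilitation and after session 20 (Vestibular assessment, Treatment); 5% significance level (Data analysis). The Protocol gives no power, effect size, SD or correlation, so it has no figure to reproduce.

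**Assumptions, not in the Protocol.** The same true gain g in both arms, from 0.2 to 0.5 SD of the score; pre-post correlation r from 0.5 to 0.7; normal data; no dropout.

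**Step 1: SD of change.** In units of the score SD this is sqrt(2(1 − r)). It is sqrt(1.0) = 1.000 at r = 0.5 and sqrt(0.6) = 0.775 at r = 0.7.

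**Step 2: time effect.** With two arms and two assessments, the time effect is a t test of the mean change on 38 df. Its noncentrality is g / SD of change × sqrt(40).
- g = 0.2, r = 0.5: 0.2 / 1.000 × 6.325 = 1.26; probability of significance 23%.
- g = 0.5, r = 0.7: 0.5 / 0.775 × 6.325 = 4.08; probability of significance 98%.

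**Step 3: group-by-time interaction.** This equals a two-sample t test on the change scores. A gain common to both arms cancels, so the rejection rate is 5% whatever g is.

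Probability of a significant result when the arms are truly identical, per outcome:

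| Shared gain (SD) | Time effect, r = 0.5 | Time effect, r = 0.7 | Group-by-time |
|---|---|---|---|
| 0 | 5% | 5% | 5% |
| 0.2 | 23% | 36% | 5% |
| 0.3 | 46% | 67% | 5% |
| 0.5 | 87% | 98% | 5% |

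Simulation (40,000 runs) at gains of 0.3 and 0.5 SD agrees: 46% to 98% for the time effect and 4.9% to 5.1% for the interaction.

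**Step 4: what the between-group contrast can detect.** For 80% power at 20 per arm, the difference is (1.960 + 0.842) × sqrt(2/20) = 0.89 SD of change by the normal approximation, or 0.91 with the t distribution. With t, power is 34% for a difference of 0.5 SD of change and 69% for 0.8 SD.

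**Step 5: the two valid contrasts are not the same estimator.** The interaction is the unadjusted difference in change, with per-patient variance 2(1 − r). ANCOVA on the second assessment has residual variance 1 − r². The ratio is (1 − r²) / (2(1 − r)) = (1 + r)/2, which is 0.75 at r = 0.5 and 0.85 at r = 0.7. ANCOVA is somewhat more precise, and the two can give different p-values on the same data.

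**The case against.** The strongest reply is that the sentence in Assessment of results only names the outcome variable. Change from baseline is an ordinary endpoint in a two-arm trial, and naming it does not rule out comparing it between arms. Repeated-measures ANOVA with two groups and two assessments normally contains the group-by-time term. Calling the study randomised and controlled, with an examiner blinded to allocation, suggests that a comparison of arms was intended. A statistical analysis plan, not available here, might name the deciding term.

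Much of this stands. A reader might infer that the Protocol formally defines success as within-patient improvement, or that it rules out a between-group test. It does neither: it sets no success rule, and the named method can carry the randomised contrast. A reader might also infer separate paired tests in each arm, and so the error of calling the strength games effective because one arm is significant and the other is not. The Protocol plans no such tests, so no figures for them are given here.

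The reply does not remove the point. Leaving a model term to a later plan is normal, but the primary criterion is already written, and the comparison it names is before with after. A later plan resting on group-by-time would supply a comparison that the Protocol's criterion does not state. The Conclusion section also leans towards the within-patient reading, because it speaks of a programme given to everyone.

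The assumed gains can fairly be challenged too. The Protocol describes a slowly progressive disease, so a shared gain of 0.5 SD is not self-evident.

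**Conclusion.** The point holds as a badly worded criterion: as written, it can be met by a time effect common to both arms, and no section makes the randomised comparison decisive. It does not show that a between-group analysis is absent or excluded.

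The range of 23% to 98% is illustrative and rests on the assumed gain and correlation. Only the size depends on them. Any real shared gain raises the chance of a significant time effect above 5% and leaves the group-by-time test at 5%. With no shared gain, both stay at 5%. The rates are per outcome, and ten tools are listed as primary.

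**What to change.** 1. In Assessment of results and Data analysis, state: *For each primary outcome, the deciding comparison is Group II minus Group I at the second assessment, estimated by ANCOVA adjusted for the baseline value, with a 95% CI.* If repeated-measures ANOVA is kept, name the group-by-time interaction instead and describe it as the unadjusted difference in change. Choose one in advance and do not present them as the same analysis.
2. Label time effects and within-group changes as descriptive.
3. Limit the Conclusion section to the added effect of the strength games over balance games alone.

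The change needs no new data or procedures. The Timeline section says that recruitment is complete, so the rewording should be dated and made before the outcome data are analysed by group. The cost is in the result: the between-group estimate may look less favourable than the within-group changes. At 20 per arm, the test on change has 80% power only for a difference of about 0.9 SD of change, so the 95% CI should be reported and a non-significant result should not be read as no effect.

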**ABC Activities-Specific Balance Confidence (ABC) scale**

The ABC scale, translated and adapted to the Brazilian population^19^, showing good quality, discriminating validity, consistency and reliability^20^.It has 16 items for assessing balance during a set of activities of daily living (ADLs) of medium difficulty^21^. The confidence for each ADL is measured by the volunteer, choosing a percentage point on a scale ranging from 0% (without confidence) to 100% (total confidence). A total greater than 80% corresponds to a high functional level, 50 to 80% moderate physical functioning and a score below 50% indicates a low functional level^22^.

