**Falls Efficacy Scale – International (FES-I)**

The FES-I is a self-administered questionnaire designed to evaluate the fear of falling during a set of activities. It is composed of 16 items scored from 1 to 4 points, with higher scores denoting a great fear of falling during a given activity. The FES-I has internal consistency of 0.96. Moreover, most items enable differentiating individuals who have suffered a fall, those who have suffered two or more falls and those who have not fallen^34^.The version validated for the Portuguese language will be used^35^.

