As a strategy to improve the adhesion to intervention protocols, will be promoted phones contacts for confirmations of treatments sessions, as well as will be available through reports the results of assessment which the participants are submitted.

The only intervention not permitted will be related to the conventional vestibular rehabilitation and virtual.

This work was supported by the authors by themselves.

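### Secondary outcome 3 promises fewer falls but is tied to no fall count, and secondary outcome 2 (spatial orientation) has no measure that isolates orientation

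*Protocol*

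**What the plan says.** The Protocol, Assessment of results, first lists ten tools as primary outcomes, each with a short statement of what it measures. It then groups the same tools under four secondary outcomes. Two of these matter here:

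- Secondary outcome 3: "Reduction in falls;evaluated by FES-I, ABC scale, VADL scale and dynamometer".
- Secondary outcome 2: "Increased spatial orientation capacity; evaluated by PPA, WHOQOL-Bref, ABC scale and MMSE".

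The tools have their own sections earlier in the Protocol. FES-I is a "self-administered questionnaire designed to evaluate the fear of falling during a set of activities". For ABC, "The confidence for each ADL is measured by the volunteer". VADL was developed "to assess the impact of dizziness and imbalance on the performance of activities of daily living". The dynamometer section describes a portable device that measures strength from a maximal isometric contraction. The MMSE section names spatiotemporal orientation among several cognitive components and describes a total score from 0 to 30.

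Under Vestibular assessment, the tools are applied twice: before rehabilitation and after the 20th session.

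**The concern.** An outcome definition has two parts, the concept and the way it is measured. In secondary outcome 3 they do not match. The concept is an event that happens to a participant between assessments. The measures are two self-rated scales of fear and confidence, a scale of dependence and a strength test. If the protocol is followed as written, an improvement on these scales could be presented as a reduction in falls although the outcome includes no fall data.

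This is fixed in the protocol and a statistical analysis plan cannot repair it, because an analysis plan cannot recover events that the outcome never called for. The label also matters to readers, since the Protocol's Conclusion section promises a definitive assessment of effectiveness.

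Secondary outcome 2 has the same kind of fault in a milder form. A change in the listed scores would be read as a change in spatial orientation, though no listed score is a measure of orientation as such.

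**Working it through.** No arithmetic applies. The protocol gives no fall rate, effect size or standard deviation, and the point depends on none. The check sets each assigned tool against the protocol's own description of it.

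**Step 1. Secondary outcome 3 (falls)**

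| Tool | What the protocol says it measures | Records falls? |
| --- | --- | --- |
| FES-I | Fear of falling, 16 items scored 1 to 4 | No |
| ABC | Self-rated confidence, 0% to 100%, over 16 activities | No |
| VADL | Effect of dizziness and imbalance on daily activities; higher scores mean more dependence | No |
| Dynamometer | Muscle strength | No |

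Result: 0 of 4.

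**Step 2. Does the FES-I link to falls rescue the outcome?** The FES-I section says that "most items enable differentiating individuals who have suffered a fall, those who have suffered two or more falls and those who have not fallen". This is a statement about discrimination: people with different fall histories answer differently. It does not say that a change in score within a person measures a change in that person's number of falls, and the score contains no count.

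**Step 3. Are the tools nearest to falls assigned here?** The protocol links three tools to risk of falls: PPA, BBS and TUG. PPA is assigned to secondary outcome 2, and BBS and TUG to secondary outcome 1. None is assigned to outcome 3. Moving them would not settle the matter, because they grade risk and do not record falls.

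**Step 4. Secondary outcome 2 (spatial orientation)**

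| Tool | What the protocol says it measures | Orientation? |
| --- | --- | --- |
| PPA | Risk of falls, through sensory and motor skills | Not described |
| WHOQOL-Bref | Perceived health and quality of life | Not described |
| ABC | Balance confidence | Not described |
| MMSE | Global cognition, 0 to 30, with spatiotemporal orientation as one component | Included, not isolated |

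Result: 3 of 4 tools are not described as measuring orientation. The fourth includes it, but the only score described is the total, and no orientation sub-score is named as the outcome.

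**The case against.** The strongest reply is that the harm is limited. Every tool is already listed as a primary outcome under its own construct: FES-I as fear of falling, the dynamometer as strength, VADL as dependence. A reader of the full results would see each scale under its proper name, and the protocol nowhere says that a lower FES-I score will be reported as fewer falls. This stands as a limit on the consequence. It does not remove the mismatch, because the secondary outcome is still defined as a reduction in falls and evaluated only by these tools.

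Four stronger readings are tempting, and the document does not support them.

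- *Falls are recorded nowhere in the trial.* The schedule (Table 2 and Figure 1) is not available, and neither the patient history nor the specific questionnaires mentioned under Assessment of results are itemised. What can be said is that outcome 3 is tied to no fall count. A falls item elsewhere would not change that definition.
- *No tool for outcome 2 touches orientation.* The MMSE section says that it does. The fault is that orientation is not separated from the total.
- *Four tools feeding one claim inflate the false-positive rate by a calculable amount.* That needs a rule that any one significant tool suffices. The protocol states no such rule and no composite, and how the tools are combined may properly be left to the statistical analysis plan.
- *Fear of falling and actual falls may move in opposite directions because more confident patients take more risks.* Nothing in the document bears on this, and the point does not need it.

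**Conclusion.** The point holds as a mismatch between label and measure in two secondary outcomes. For outcome 3, none of the four assigned tools measures falls, so the data cannot support a conclusion that falls were reduced. For outcome 2, three of the four tools are not described as measuring orientation and the fourth includes it only within a global total, so a claim about orientation is not supported as the outcome is now defined.

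The conclusion rests only on the protocol's descriptions of its own instruments and on the assignment of tools under Assessment of results. It assumes no error rate, effect size or rule for combining tools. The primary outcomes, which name each tool by its construct, are not affected by this point. The remedy is a correction of labels and of what may be concluded.

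**What to change.** - **Secondary outcome 3.** Rename it by what its tools measure: fear of falling (FES-I), balance confidence (ABC), dependence in daily activities (VADL) and muscle strength (dynamometer). Add a sentence that no conclusion on reduction in falls will be drawn from these tools.
- **Secondary outcome 2.** Either name the MMSE orientation items as the measure of orientation, or rename the outcome by what its four tools measure.

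Both changes are to wording, cost nothing and can be made at any time before reporting. Each tool is already a primary outcome in its own right, so no separate reporting has to be added.

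If a falls claim is wanted, falls would have to be recorded directly. The Management section already plans "phones contacts for confirmations of treatments sessions", and a question on falls could be added there only if participants are still in treatment. The Timeline section says that recruitment is complete and that treatment was expected to end by July 2021, so this may no longer be possible. Falls before the change would be missed, and the calls are not stated to be made by the blinded examiner specified under Assessment of results. Such data should therefore be reported as descriptive only.
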